## Abstract

**Background:**

Schools are natural environments in which to enhance young people’s social and emotional skills, mental health, and contact between diverse groups, including students from refugee and immigrant backgrounds. A layered or tiered provision of services is recommended as it can be effective to meet the needs of war-affected adolescents who variably show mental health problems (such as posttraumatic stress disorder (PTSD)). The current protocol describes the study design for a multi-layered intervention model. The study will test the effectiveness of two interventions: a teacher-training intervention In-Service Teacher Training (INSETT) combined with targeted cognitive-behavioral treatment-based Teaching Recovery Techniques (TRT) and a classroom-focused preventive intervention Peer Integration and Enhancement Resources (PIER). We analyze, first, whether the interventions are effective in decreasing psychological distress and increasing positive resources, i.e., prosocial behavior and resilience among refugee and immigrant students. Second, we analyze which student-, school-, and parent-related factors mediate the possible beneficial changes. Third, we look at which groups the interventions are most beneficial to.

**Methods:**

A three-arm cluster RCT with parallel assignment, with a 1:1:1 allocation ratio, is applied in 16 schools that agreed to participate in the Refugees Well School interventions and effectiveness study. Schools were randomized to three conditions of two active interventions and a waiting list control condition. Students, their parents, and teachers in intervention and control schools participated in the study at baseline before the interventions, after the interventions, and at 6 to 12 months after the interventions. The primary effectiveness criterion variables are psychological distress (SDQ) symptoms, resilience (CYRM-12), and prosocial behavior (SDQ).

**Discussion:**

The current study presents a recommended universal approach of layered interventions aiming to reduce psychological distress and increase resilience among refugee and immigrant students. A combination of promotive, preventive, and targeted interventions may offer a holistic, ecological intervention package for schools to better address the needs of the whole group.

**Trial registration:**

ISRCTN ISRCTN64245549. Retrospectively registered on 10 June 2020

## Administrative information

Note: the numbers in curly brackets in this protocol refer to SPIRIT checklist item numbers. The order of the items has been modified to group similar items (see http://www.equator-network.org/reporting-guidelines/spirit-2013-statement-defining-standard-protocol-items-for-clinical-trials/).

Schools are natural environments to provide psychosocial support for minors [10–13]. Nevertheless, targeted school-based interventions have been criticized for their inability to cover the full range of multi-faceted problems refugee youth face in their everyday life [14–17]. Multi-layered or triad intervention models may match more accurately than single interventions with the needs of adolescents exposed to traumatic war experiences and refugee-related stress [18–20]. The present protocol describes the study design for a school-based multi-intervention model; combined interventions aim to promote resilience, prevent mental health problems, and reduce symptoms of an ongoing disorder especially among refugee and immigrant adolescents. The study will evaluate the effectiveness of these promotive, preventive, and focused interventions. Further, it will examine student-, school-, and home-related factors that may mediate or moderate the effect of interventions on student well-being.

## Effectiveness of multi-layered and targeted psychosocial interventions among refugee youth

Multi-layered intervention models typically involve three types of interventions: promotive universal psychosocial support interventions, preventive interventions provided to whole schools or classrooms, and targeted cognitive-behavioral therapies (CBT) [19, 21]. Although this approach is increasingly recommended, only three studies were detected to have evaluated the effectiveness of multi-layered interventions [22–24]. The results seem promising but are rather inconsistent and lack statistical power.

The first study [22] presented a practice-driven evaluation of a multi-layered community-based care package in four war-affected countries. Client satisfaction was high, and mental health problems were reduced moderately. Yet, service providers reported significant levels of distress related to service delivery. The second study [23] assessed the effectiveness of a school-based mental health program for traumatized immigrant children and adolescents in the USA. All students were provided with an array of clinical services including CBT, supportive therapy, and coordinating services. A trauma-focused (TF) CBT was implemented with a subset of students. The greater quantity of CBT and supportive therapy was associated with increased psychosocial functioning, and a greater quantity of coordinating services was associated with decreased PTSD symptoms. TF-CBT was associated with both improved functioning and decreased PTSD symptoms. The results thus suggest that the comprehensive school-based model was effective and that different service components resulted in specific outcomes. The third study [24] examined the effectiveness of a four-tiered program for young Somali refugees in the USA. The intervention elements included community resilience building, school-based universal early intervention, and targeted treatment for students suffering from severe psychological distress. The authors reported that students across all tiers of the program demonstrated improvements in mental health and resources. Yet, the sample size per tier was small, and comparative analyses between tiers were not possible to conduct.

School- or classroom-based promotive and preventive interventions are often delivered through teachers’ education. Developmental theories for ecological systems suggest enhancing teachers’ cultural competence and increasing their awareness of the impact of trauma on learning [25]. Teachers have a pivotal role in helping refugee and migrant students to improve their mental health [26–30].

Focused psychosocial school interventions have shown a beneficial impact on trauma-affected refugee and immigrant children. This has been indicated by decreased PTSD, depressive, and anxiety symptoms and functional and peer problems [20, 31–33]. However, effect sizes vary between moderate and very high across studies, and also null results have emerged [34–36]. Cognitive-behavioral treatments with trauma-focus (TF-CBT) belong to the group of focused psychosocial interventions. They can involve several therapeutic elements such as learning to process past traumatic events verbally or multi-modally, expressing painful emotions, and constructing a new narrative from children’s shattered experiences in a new and safe environment. Other common intervention elements are the use of various creative techniques including drama, music and drawing, shared activities within the classroom, and interaction with peers [37].

School-based interventions for refugee and immigrant children and adolescents can attune anxiety and depression and reduce PTSD symptoms [32, 38]. Interventions using CBT-based methods have been shown especially effective with trauma-affected children [39]. Interventions with creative elements of writing, drawing, or drama are found to decrease immigrant children’s and adolescents’ mental health problems [38] and to increase positive resources such as effective coping and hope [40].

In the current study, the promoting intervention is In-Service Teachers’ Training (INSETT) which aims at enhancing teachers’ cultural competence and self-efficacy through training. Teaching Recovery Techniques (TRT) is the targeted, TF-CBT-based intervention. A classroom-based, preventive intervention called Peer Integration and Enhancement Resources (PIER) provides tools to increase and reinforce multi-cultural friendships and to create a safe and welcoming classroom environment for adolescents from migrant and refugee backgrounds.

## Mediating and moderating effects of psychosocial interventions

Four mechanisms of change were found strong empirical evidence in the context of psychosocial interventions aiming to improve well-being, mental health, and resilience among children affected by war [41]. The first mechanism was *building family and caregiver capacity*, which involved support to families, caregivers, and practitioners to enable them to enhance child well-being through psychoeducation, dialog, and self-care. The second mechanism was *strengthening family and caregiver relationships with children facing traumatic stress*. Strengthening relationships was especially important in collectivist cultures where family relationships form a core resource. The third mechanism concerned children’s capacities: *improving active problem solving, effective coping, and mastery of traumatic experiences*. The fourth mechanism was *therapeutic rapport in targeted interventions*, and it was indicated by trusting therapeutic relationships and a safe environment for disclosure of traumatic experiences. It is noteworthy that only moderate evidence was found for TF-CBT-based mechanisms, such as processing trauma through reconstructing harmful cognitions, framing narratives, playing, or learning effective regulation of painful emotions. Also, interventions focusing on strengthening community and cultural resources, values, and rituals did not gain high-quality support among war-affected children.

A study based on the ecological resilience framework found that increased social support mediated the intervention impact resulting in reduced PTSD symptoms. Change in hope or coping strategies did not mediate treatment effects on PTSD symptoms [42]. Using metadata, one study [43] found only psychosocial functioning (in personality, social, and academic domains) to mediate intervention impact on mental health among children in low-resource humanitarian settings. Instead, the hypothesized effective coping strategies, social support, or positive attitudes of hope were not significant mediators of intervention impacts.

## Objectives

The first aim of this research project is to test whether two school-based psychosocial intervention arms, (a) the combined In-Service Teacher Training (INSETT) and Teaching Recovery Techniques (TRT) and/or (b) the Peer Integration and Enhancement Resource (PIER), are effective in improving the mental health among refugee, migrant, and Finnish native adolescents. The criteria for intervention effectiveness are reducing psychological distress (internalizing and externalizing symptoms) and increasing prosocial behavior and resilience compared to adolescents in control schools. The second aim is to examine which adolescent- and/or school-related factors could explain the effectiveness of these two arms of school-based psychosocial interventions (mediation analysis). Third, we analyze whether the adolescent- and family-related preconditions differ in the effectiveness of these two intervention arms (moderation analysis).

The research questions and hypotheses are as follows:
Do psychosocial school interventions have a positive effect on the mental health of immigrant adolescents? In more detail, the aim is to compare the impact of INSETT+TRT and PIER to the waiting list control group on internalizing and externalizing symptoms and prosocial behavior and resilience.
We hypothesize that internalizing and externalizing symptoms will decrease statistically significantly only among adolescents participating in the INSETT+TRT and PIER interventions and not in the control group from baseline (T1) to 6-month (T2) and 12-month (T3) follow-ups.We hypothesize that prosocial behavior and resilience will increase only among adolescents participating in the two arms of interventions and not in the control group.Do different adolescent- and school-related factors explain (mediate) the effects of the INSETT and PIER interventions on adolescent mental health?
Concerning INSETT, we hypothesize that participation of teachers increases their multi-cultural awareness, sense of self-efficacy, and work engagement and decreases their work stress, which in turn are associated with the decreased internalizing and externalizing symptoms and increased prosocial behavior and resilience among the adolescents.We hypothesize that adolescents’ participation in PIER intervention is associated with their increased social support, feeling of belongingness, number of inter-ethnic friendships, and satisfaction on friendships, which in turn is associated with decreased internalizing and externalizing symptoms and increased prosocial behavior and resilience.We hypothesize that adolescents’ participation in TRT intervention is associated with decreased PTSD symptoms of intrusion and avoidance, which in turn is associated with decreased internalizing and externalizing symptoms and increased prosocial behavior and resilience.How do parent- and adolescent-related factors moderate the effectiveness of the two arms of school-based psychosocial interventions of INSET+TRT and PIER?
We hypothesize that good parental mental health and parents’ high sense of competence and confidence in parenting are associated with a statistically significant positive intervention-induced change in adolescents’ mental health (i.e., decreased internalizing and externalizing symptoms and increased prosocial behavior and resilience).We hypothesize that adolescents who report the low frequency of daily stressors and low perceived discrimination show more statistically significant positive intervention-induced change in their mental health (i.e., decreased internalizing and externalizing symptoms and increased prosocial behavior and resilience).

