## Trial design

The study is a three-arm clustered parallel assignment, quasi-randomized, controlled trial (RCT) comparing INSETT+TRT and PIER to the wait list control group. The cluster is designed by the school. The schools were allocated into intervention groups or a control group using quasi-randomized design: The voluntary schools were first grouped based on whether they offered an introductory class or not. The TRT is targeted at recently arrived youth with a refugee background, and the PIER is targeted at mixed classes. The schools in the two groups were then randomly allocated to either intervention or control conditions using a random number generator [44]. The allocation aimed at equal numbers of schools in each condition. Due to the low participation rate, recruitment of schools was continued, which resulted in three additional schools all with introductory classes. The three additional schools were thus randomized either into the INSETT+TRT or control group. Blinding of participants, intervention providers, outcome assessors, or data analysts was not possible due to the explicit nature of interventions and a low number of project members. The decisions of data collection, recruitment, and training are discussed with other partners in the RefugeesWellSchool consortium but allowing each country to adopt the processes in the national framework. The control schools will receive the INSETT intervention toolkit after the research part of the project has ended. The trial aims to follow SPIRIT guidelines in reporting. Table 1 presents the SPIRIT figure, and the checklist can be found as an attachment.

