## Study setting and participants

Power calculations were conducted before the data collection started. With alpha set at 0.05, power at 0.80, and rho = 0.05 (the intra-cluster correlation), a sample size of at least 40 clusters (i.e., schools) with 25 youths each was identified as necessary. Therefore, 500 youths per study arm (i.e., intervention or wait list control) were needed, resulting in 1500 total participants. To account for an expected drop-out rate of 20%, 1800 youths would have been recruited in total. To facilitate the recruitment of so many participants, recruitment was split between the Finnish study team and our team partners in Sweden.

The interventions were implemented in lower secondary schools with grades 7–9 and/or introduction classes for newcomer youth. We focused on immigrant youth who have resided in Finland for less than 6 years. Figure 1 presents the flowchart of the recruitment. Seventeen schools expressed their interest in participating in the study, but after allocation, one school dropped out. According to the randomization, eight schools were allocated into the INSETT+TRT intervention, three schools were allocated into PIER, and five schools served as waiting list controls. Also, Fig. 1 reports the numbers of students, teachers, and parents who answered the survey in the first round of data collection.

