The school staff delivering the PIER participated in a 2-day training. The first day included practicing each intervention session and going through the resource material. The second day included sharing experiences and valuable ideas to improve the intervention.

*Teaching Recovery Techniques (TRT)* is a TF-CBT-based, manualized group treatment developed by the Children and War Foundation [48]. The core aim of this intervention is to create a sense of safety and increase feelings of competence and shared hope. In more detail, the aims are to reduce PTSD symptoms of intrusion, avoidance, and hypervigilance; increase resilience; stabilize trauma reactions; and provide practical techniques and strategies to deal with traumatic memories, physical and behavioral arousal, and withdrawal. Treatment elements include psychoeducation (in playful and multi-modal ways), normalizing reactions to trauma, working with nightmares, mastering intrusive memories and trauma reminders with framing techniques, and dealing with avoidance and arousal with scaling techniques. Homework such as sleep hygiene or reflective observation of trauma reminders is an essential part of the TRT.

The TRT consists of five sessions of 90 to 120 min including skills training, rehearsal, and homework, and the handbook provides each session with several tools, techniques, and procedures. The two sessions for parents or caregivers include information about various responses to traumatic events and effective coping strategies. School personnel delivering the TRT participate in 2-day intensive training provided by a licensed trainer either from the Children and War Foundation or from Finland. Qualified trauma psychologists offer work counseling to TRT group leaders during the intervention.

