In the core model (Fig. 2), there are two latent state variables, measuring true scores of PRE- and POST-intervention levels of the outcomes. The PRE-intervention state is indicated by the measured T1 variable without time-related measurement error because there is only one measurement point. In the case of POST-intervention state, there are two indicators, enabling the modeling of measurement error. The loadings of the indicators in the measurement part of the model are fixed to 1’s, meaning that the trajectory from T1 to T3 has the same shape for every individual. Only the level of PRE-intervention state and the difference between PRE- and POST-intervention states are random so that the means and variances of these variables within and between the clusters can be estimated. As predictors of the POST-intervention state, our model specifies the PRE-intervention state (path coefficient *a*, which is anticipated to be negative due to floor and ceiling effects), a dummy for intervention/control group membership (direct effect *c*), and potential mediating variables (path coefficient *e*, implying indirect effect *d*e* for intervention-control-group difference). The covariance between the PRE-intervention state and the dummy for intervention/control group membership (parameter *b*) is supposed to be 0, indicating that the randomization was successful. Moderation mechanisms are investigated by estimating the model simultaneously in groups created according to categorized moderator variables (multi-group SEM). Finally, the simple estimates of total intervention effects are calculated from a model without mediators and moderators (parameter *c* divided by the variance of POST-intervention latent variable, giving an equivalent to Cohen’s *d*).

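### INSETT and TRT are allocated only as one arm, so mediated effects of that arm cannot be credited to INSETT or to TRT separately, as research question 2, its hypotheses and the Fig. 2 labels do

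*Protocol article*

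**What the plan says.** The arms are clear. Objectives names the two active conditions as "a) the combined In-Service Teacher Training (INSETT) and Teaching Recovery Techniques (TRT) and/or (b) the Peer Integration and Enhancement Resource (PIER"), and Trial design describes the study as "comparing INSETT+TRT and PIER to the wait list control group". Study setting and participants gives the result of allocation: "eight schools were allocated into the INSETT+TRT intervention, three schools were allocated into PIER, and five schools served as waiting list controls".

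The mediation part of Objectives is worded differently. Research question 2 asks which "factors explain (mediate) the effects of the INSETT and PIER interventions on adolescent mental health", so INSETT is named without TRT. The hypotheses under it then split the arm. One concerns INSETT and runs through teachers' multicultural awareness, self-efficacy, work engagement and work stress. Another concerns TRT and runs through PTSD symptoms: "participation in TRT intervention is associated with decreased PTSD symptoms of intrusion and avoidance". The Fig. 2 legend follows this split, with seven teacher mediators listed under INSETT and CRIES-8 under TRT.

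The core-model text in Analytic strategy, after Fig. 2, has as its exposure "a dummy for intervention/control group membership". The legend codes intervention status as control, INSETT+TRT or PIER. No indicator for a single component is described.

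**The concern.** Two hypotheses are stated about components, but the design varies only the pair. If teacher scores improve in the INSETT+TRT arm, the protocol's labels credit INSETT. If CRIES-8 scores fall, they credit TRT. The design gives no allocated contrast that supports either step.

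It might be thought that the choice of mediators separates the components, with teacher variables belonging to the teacher training and trauma symptoms to the trauma treatment. The section The interventions does not support that. TRT is delivered by staff: "School personnel delivering the TRT participate in 2-day intensive training", and its group leaders receive work counselling from trauma psychologists while it runs. Both could change teachers' self-efficacy or stress. INSETT, in turn, is expected to promote the mental health of trauma-affected students, which could change CRIES-8.

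The attribution has practical weight because components are handed on singly. Waiting-list schools are to receive INSETT without TRT, and Dissemination plans open-access manuals for INSETT and PIER. A bundle effect credited to INSETT would appear to support INSETT on its own, which no school was allocated during the study.

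**Working it through.** No figure in the protocol depends on this point, so there is none to reproduce. The question is which effects the allocation identifies.

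**Inputs.** The arms and school counts are 8 INSETT+TRT, 3 PIER and 5 control, 16 in total (Study setting and participants). The exposure is arm membership, and the indirect effect is d × e for the intervention-control difference (Analytic strategy). Control schools receive INSETT in October 2020 (Recruitment and sampling), after data collection ended in September 2020 (Trial status), so no later INSETT-only contrast arises.

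**Step 1: design matrix.** Code each arm as (intercept, INSETT, TRT, PIER):

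| Arm | Intercept | INSETT | TRT | PIER |
|---|---|---|---|---|
| Control | 1 | 0 | 0 | 0 |
| INSETT+TRT | 1 | 1 | 1 | 0 |
| PIER | 1 | 0 | 0 | 1 |

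The INSETT and TRT columns are identical. The matrix has rank 3 for 4 parameters. A contrast is estimable if adding it as a row leaves the rank at 3:

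- INSETT+TRT versus control, (0,1,1,0): estimable.
- PIER versus control, (0,0,0,1): estimable.
- INSETT alone, (0,1,0,0): not estimable.
- TRT alone, (0,0,1,0): not estimable.

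**Step 2: indirect effects.** Let d be the effect of allocation to INSETT+TRT on a mediator and e the path from that mediator to the outcome. If the components act additively on the mediator, d = d(INSETT) + d(TRT), and the indirect effect is d × e = [d(INSETT) + d(TRT)] × e. The data identify only the sum in brackets. Crediting a teacher-mediated effect to INSETT requires d(TRT) = 0 for the teacher variables. Crediting a CRIES-8-mediated effect to TRT requires d(INSETT) = 0 for CRIES-8. The protocol states neither condition, and its own description of the interventions gives reason to doubt both. An interaction between the components would add a third term that cannot be separated either.

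**Step 3: TRT as delivered.** The protocol's Discussion reports that TRT implementation failed in five schools whose groups were planned for spring 2020. TRT belongs only to the INSETT+TRT arm, so by inference these are five of its eight schools (5/8 = 62.5%). Unless they ran other TRT groups, they received INSETT without TRT while still coded INSETT+TRT. This split followed school scheduling, not allocation, so it does not validly separate the components. It does mean that the arm effect is one of allocation to the package.

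**Step 4: all three layers.** The contrast (0,1,1,1) is estimable only as the sum of the two arm effects, assuming no interaction between PIER and the pair. With an interaction term it is not estimable, because no arm contains all three. The sum is also doubtful because schools were grouped by introductory class before allocation, and TRT and PIER target different students (Trial design).

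**The case against.** The strongest reply is that the protocol already works at arm level where it matters. The general statement of the second aim in Objectives asks what explains the effectiveness of the two arms, and the core model defines d × e for the intervention-control difference. The hypotheses can then be read as expected pathways of the arm, and the TRT hypothesis claims only an association with participation. Bundling is also a legitimate package design.

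Most of this stands. A reader might infer that the second aim cannot be answered by this design at all. The documents do not support that: the indirect effects of the INSETT+TRT arm through each pathway are estimable, and an association with actual TRT participation could be reported as a non-randomised finding. What the reply does not remove is the component attribution written into question 2, the two hypotheses and the Fig. 2 legend. Nor does any section say that the components cannot be separated.

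A reader might also infer that the trial claims to test a three-layer package, because the Abstract's Discussion says "A combination of promotive, preventive, and targeted interventions may offer a holistic, ecological intervention package for schools". That sentence is hedged, and no objective, hypothesis or model parameter stands behind it; the Abstract's Background says that two interventions are tested. This is a matter of framing and deserves a wording note only.

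Finally, it would be too strong to say that only three intervention packages were observed. Three were allocated, but the TRT failure may have produced a fourth in practice.

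**Conclusion.** The point holds for attribution to components. Zero of 16 schools were allocated INSETT alone or TRT alone, and the two indicators are fully aliased, so no allocated contrast supports a mediated effect of either. Mediated effects of the eight-school INSETT+TRT arm against the five control schools can be estimated, subject to the usual assumptions about the mediator-outcome path, and should be reported as such.

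The conclusion rests on two readings: that the fitted exposure is arm membership, as Analytic strategy states, and that either component could plausibly affect either mediator set, as The interventions indicates. That the five schools where TRT failed lie in the INSETT+TRT arm is an inference from the arm definitions.

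The primary arm-level comparisons are unaffected. This is a correction to the claims made under a secondary aim, worth making because it limits what the trial may conclude about each component.

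**What to change.** 1. Restate research question 2, the INSETT and TRT hypotheses and the Fig. 2 mediator labels as indirect effects of allocation to INSETT+TRT versus control: one through teacher variables, one through CRIES-8, with no attribution to a single component.
2. State beside them that TRT implementation failed in five schools, so the arm effect is that of allocation to the package and not of full delivery. Label any comparison by TRT actually received as non-randomised and exploratory.
3. Limit conclusions to the two packages tested, INSETT+TRT and PIER. As a wording note, say that no arm combines the promotive, preventive and targeted layers.

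The cost is rewording and narrower claims; no new data or models are needed.

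Two additions may seem natural, but I would not ask for them. Running the teacher mediators in the PIER arm as a check for a general training effect would not be diagnostic: there are three PIER schools, and PIER's own content on identities, migration and racism could change teachers' attitudes. Requiring all mediators in one model would put up to 7 + 1 = 8 mediators on 8 + 5 = 13 schools, which is not a free change and does not separate the components.
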